### 3 SELECTION OF PARTICIPANTS

There will be **no exceptions** to eligibility requirements at the time of enrolment. Questions about eligibility criteria should be addressed prior to attempting to enrol the participant.

The eligibility criteria are the standards used to ensure that only medically appropriate participants are considered for this study. Participants not meeting the criteria should not join the study. For the safety of the participants, as well as to ensure that the results of this study can be useful for making treatment decisions regarding other patients with similar health statuses, it is important that no exceptions be made to these criteria for admission to the study.

Participants will be considered eligible for enrolment in this trial if they fulfil all the inclusion criteria and none of the exclusion criteria as defined below.

#### 3.1 PARTICIPANT INCLUSION CRITERIA

1. Healthy adults from the following age ranges:
  - a. For the dose escalation and evaluation, aged 18-45 years on the day of screening
  - b. For the expanded safety evaluation, aged 18-75 years on the day of screening
2. At similar risk of acquiring SARS-CoV-2 infection to the general population
3. Willing and able to provide written informed consent
4. If female and of childbearingi potential, willing to use a highly effective methodii of contraception from screening until 18 weeksiv after last injection
5. If male and not sterilised, willing to avoid impregnating female partnersiii from screening until 18 weeksiv after last injection
6. Willing to avoid all other vaccines from within 4 weeks before the first injection through to 4 weeks after the second injectionv
7. Willing and able to comply with visit schedule, complete online diaries and provide samples
8. Willing to grant authorised persons access to his/her trial-related medical record and GP records either directly or indirectly

i A woman will be considered of childbearing potential following menarche and until becoming post-menopausal (no menses for 12 months without an alternative medical cause) unless permanently sterile. Permanent sterilisation methods include hysterectomy, bilateral salpingectomy and bilateral oophorectomy. A post-menopausal state is defined as no menses for 12 months without an alternative medical cause.

ii The following methods are considered highly effective:

- combined (estrogen and progestogen containing) hormonal contraception associated with inhibition of ovulation – oral, intravaginal or transdermal;
- progestogen-only hormonal contraception associated with inhibition of ovulation – oral, injectable or implantable
- intrauterine device (IUD);
- intrauterine hormone-releasing system (IUS);
- bilateral tubal occlusion;
- vasectomised partner, where the vasectomised partner has received medical assessment of the surgical success; and
- sexual abstinence, defined as refraining from heterosexual intercourse – must be the preferred and usual lifestyle of the participant.

iii Through the use of condoms or sexual abstinence (see definition in footnote ii above)

iv Nonclinical studies of saRNAs [48] showed maximal expression of the vaccine immunogen at 7 days post-immunisation, approaching baseline by 3 weeks post-immunisation, with some residual very low expression seen out to 9 weeks. Biodistribution studies with LNP-nCoVsaRNA are planned, but in the absence of data we wish to take a conservative approach to the contraception period, and require an 18-week washout period.

v The exception is the flu vaccine, which participants may have – provided they have it at least 7 days before or after a study vaccination. It is recommended that participants have an up to date vaccination status for any required immunisations.

### 3.2 PARTICIPANT EXCLUSION CRITERIA

1. Pregnant or lactating
2. Has a significant clinical history, physical finding on clinical examination during screening, or presence of a disease that is active or requires treatment to control it, including cardiac, respiratory, endocrine, metabolic, autoimmune, liver, neurological, oncological, psychiatric, immunosuppressive/immunodeficient or other disorders which in the opinion of the investigator is not compatible with healthy status, increases the risk of severe COVID-19, may compromise the volunteer's safety, preclude vaccination or compromise interpretation of the immune response to vaccine. Individuals with mild/moderate, well-controlled comorbidities are allowed.
3. History of COVID-19 infectioniii
4. History of anaphylaxis or angioedema
5. History of severe or multiple allergies to drugs or pharmaceutical agents
6. History of severe local or general reaction to vaccination defined as:
  - a. **local:** extensive, indurated redness and swelling involving most of the arm, not resolving within 72 hours
  - b. **general:** fever  $\geq 39.5$  °C within 48 hours; bronchospasm; laryngeal oedema; collapse; convulsions or encephalopathy within 72 hours
7. Ever received an experimental vaccine against COVID-19
8. Receipt of any immunosuppressive agents within 18 weeks of screening by any route other than topical
9. Detection of SARS-CoV-2 antibodies prior to enrolmenti
10. Detection of antibodies to hepatitis C
11. Detection of antibodies to HIV
12. Grade 1ii and above abnormalities in routine laboratory parameters (see [Table 5](#)) using the FDA toxicity table Toxicity Grading Scale for Healthy Adult and Adolescent Volunteers Enrolled in Preventive Vaccine Clinical Trials, taking account of local laboratory reference ranges. <https://www.fda.gov/media/73679/download>
13. Participating in another clinical trial with an investigational drug or device, or treated with an investigational drug within 28 days of screening.
14. Has received an immunisation within 28 days of screening
  - i Only in participants enrolled into the dose escalation and dose evaluation cohorts A1, A2, B1, B2
  - ii Trace of protein and/or blood on dipstick urinalysis and ALT/AST  $\leq 1.2 \times$  ULN are not exclusion
  - iii This exclusion criterion applies at all sites with the exception of the St Mary's Hospital site, which will preferentially enrol participants known to have infection-induced SARS-CoV-2 antibodies prior to enrolment

### 3.3 NUMBER OF PARTICIPANTS

414 participants.

### 3.4 CO-ENROLMENT GUIDELINES

Co-enrolment in previous or future trials can be reviewed on a case basis (see [Section 4.2](#)).

### 3.5 SCREENING PROCEDURES & PRE-RANDOMISATION INVESTIGATIONS

Informed consent to enter into the trial must be obtained from participants after explanation of the aims, methods, benefits and potential hazards of the trial and *before* any trial-specific procedures are

performed or any blood is taken for the trial. Participants must be willing and able to provide informed consent (as detailed in [Section 3.1](#)). This therefore excludes: persons deprived of their liberty by a judicial or administrative decision, persons under psychiatric care and persons admitted to a health or social institution for purposes other than research; and persons who are the subject of a legal protection measure or who are unable to express their consent.

It must be made completely and unambiguously clear that the participant is free to refuse to participate in all or any aspect of the trial, at any time and for any reason, without incurring any penalty or affecting their treatment.

Signed consent forms must be kept by the investigator and documented on the case report form (CRF) and a copy given to the participant. With consent, the participant's GP will be sent a letter informing them of their patient's intention to participate in the trial, and requesting that they corroborate their patient's medical history. Corroboration may also be obtained via the study team accessing patient's electronic care summaries, GP and other medical records from local systems, or via participants bringing their medical care summaries from their GP to the study team. However, participants may be enrolled based on the medical history given at the screening visit only, at the investigator's discretion.

Investigator sites registered with The Overvolunteering Protection System (TOPS) should run checks for the purposes of assessing exclusion criterion 13.

Screening procedures and investigations are listed in [Tables 2 and 3](#) and covered in more detail in [Section 6](#).

## 4 REGISTRATION & RANDOMISATION

### 4.1 RANDOMISATION PRACTICALITIES

Further details on the process of randomisation can be found in [Section 9.1](#).

Randomisation will only take place at one centre, and only for the first dose evaluation, with a paper randomisation list at the investigator site.

Investigator site staff will know the allocated dose, but participants and laboratory staff will not.

### 4.2 CO-ENROLMENT GUIDELINES AND REPORTING

Co-enrolment in other clinical trials with an investigational or non-investigational drug or device is not permitted, and individuals who have been treated with an investigational drug within 28 days before the first vaccination will be excluded.

All other co-enrolments should be discussed with MRC CTU at UCL and the Chief Investigator and will be decided on a case by case basis.

## 5 TREATMENT OF PARTICIPANTS

### 5.1 INTRODUCTION

Participants in the dose escalation and evaluation will each receive two IM doses of LNP-nCoVsaRNA (0.1, 0.3, 1.0, 2.5, 5 or 10 µg), into the deltoid muscle at Week 0 and Week 4 (see [Table 4](#)).

Participants in the expanded safety evaluation will each receive two IM doses of LNP-nCoVsaRNA: 1.0 µg at Week 0; and 1.0 µg at Week 4 or 2.5, 5 or 10 µg at Week 14, as recommended by the Trial Steering Committee, into the deltoid muscle (see [Table 4](#)).

Storage, dispensing, reconstitution and dilution of IMP, the volume for injection and method of administration for each dose level will be described in the COVAC1 Pharmacy Manual.

Table 4: **Vaccine candidates and dispensing schedule**

| Study component                | Route | Week 0                  | Week 4 or 14*                                 |
|--------------------------------|-------|-------------------------|-----------------------------------------------|
|                                |       | Visit 2                 | Visit 5                                       |
| Dose escalation and evaluation | IM    | 0.1 µg
LNP-nCoVsaRNA | 0.1 µg
LNP-nCoVsaRNA                       |
|                                | IM    | 0.3 µg
LNP-nCoVsaRNA | 0.3 µg
LNP-nCoVsaRNA                       |
|                                | IM    | 1.0 µg
LNP-nCoVsaRNA | 1.0 µg
LNP-nCoVsaRNA                       |
|                                | IM    | 2.5 µg
LNP-nCoVsaRNA | 2.5 µg
LNP-nCoVsaRNA                       |
|                                | IM    | 5 µg
LNP-nCoVsaRNA   | 5 µg
LNP-nCoVsaRNA                         |
|                                | IM    | 10 µg
LNP-nCoVsaRNA  | 10 µg
LNP-nCoVsaRNA                        |
| Expanded Safety                | IM    | 1.0 µg
LNP-nCoVsaRNA | 1.0 µg or
2.5, 5 or 10 µg
LNP-nCoVsaRNA |

\*The timing of the second vaccination in the expanded safety cohort is 4 or 14 weeks after the first vaccination

#### 5.1.1 LNP-nCoVsaRNA VACCINE

The LNP-nCoVsaRNA vaccine candidate is manufactured by Polymun Scientific Immunbiologische Forschung GmbH, Klosterneuburg, Austria in accordance with European GMP on behalf of the sponsor, who is also responsible for the product development.

LNP-nCoVsaRNA will be supplied to the sites free-of-charge by the sponsor's distribution partner, PCI Pharma Services. PCI will supply the IMP with COVAC1-specific labels, according to GMP.

The vaccine will be supplied in glass vials at a concentration of 500 µg RNA per mL, with a 100 µL fill volume. It will be supplied with a sterile dilution buffer for reconstitution – phosphate buffered

saline in glass vials with an 18 mL fill volume. The vaccine is a liquid suspension with a white to off-white, appearance.

This vaccine candidate is not classified as a genetically modified organism (GMO).

#### 5.1.2 ADMINISTRATION

Vaccine should be administered intramuscularly in the deltoid muscle of the upper arm using a 23G 1-inch needle. The participant may choose which arm.

Participants will be observed for at least 60 minutes after the injection.

#### 5.1.3 STORAGE

The LNP-nCoVsaRNA vaccine will be stored in a secure, limited access storage area under the specified storage requirements. The vaccine will be stored according to the Pharmacy Manual and the arrangements will be reviewed at site initiation.

#### 5.1.4 DISPENSING

The pharmacist, or other person delegated by the PI, will ensure that the vaccines are dispensed in accordance with the protocol and Pharmacy Manual and local procedures as appropriate. Local working instructions will be reviewed at site initiation, if applicable.

A vaccine accountability log will be kept to record the identification of the participant to whom the vaccine was given and the date they received it. Any damaged or unused vials that are returned will also be documented. The log will be checked during the monitoring visits and at the end of the trial.

#### 5.1.5 SCHEDULE MODIFICATIONS & INTERRUPTIONS

Target visit dates (based on the enrolment date) should be adhered to as far as possible, based on the allowable window (detailed in [Tables 2 and 3](#) ).

The schedule may be interrupted if a participant has symptoms or signs on the day of scheduled injection, and the investigator considers it best to defer the injection. A temperature over 37.5 °C would prevent injection on the day. Clinicians should consult the PI/Medical Delegate if there are any Grade 1 (mild) symptoms or signs listed in [Table 5](#), or any symptoms suggestive of COVID-19. The participant will be asked to return for review within the ideal window period of the scheduled injection. Provided the injection is administered during the window period outlined in the paragraph below for missed visits, this will not be a protocol deviation.

The PI or Medical Delegate should interrupt the vaccine schedule and inform MRC CTU at UCL within 24 hours using the safety email (see [section 7](#)) if there is a confirmed:

- (1) Grade 3 (severe) or worse solicited adverse event that has persisted for more than 72 hours regardless of relationship or
- (2) other Grade 3 (severe) or worse adverse event that is possibly, probably or definitely related to vaccine or
- (3) serious adverse reaction regardless of grade

The Chief Investigator/Delegate may recommend further investigations or referral to an independent expert to support the clinical management of the participant. Such events are highly likely to result in discontinuation, but a decision to resume will be taken by the PI with the participant, and only with the approval of the independent members of the TSC.

Injections for all participants will be paused pending a review of all safety data by the Trial Steering Committee if two participants out of 20, and the equivalent (10%) thereafter develop persisting Grade

3 (severe) adverse reactions within 7 days of immunisation, or any participant experiences a serious adverse reaction at any time. If vaccinations are paused in all participants, a substantial amendment must be submitted to the competent authorities. Likewise, approval from the competent authorities must be sought before the study can be resumed.

Participant visits will continue during a pause. Missed injections will be rescheduled and the remaining study visits rescheduled/repeated accordingly.

All visits will be suspended for any participant with suspected, probable or confirmed COVID-19 until they are out of necessary quarantine and until the diagnosis can be confirmed by appropriate testing.

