| Urinary pregnancy test (WOCP only)                                   | X         | X      |       |         |          |                  |                  | X                      |                 |                 |                 |                 | X               |                |           |
| Blood for central serum immunogenicity assays                        |           | 6 mL   |       | 6 mL    | 6 mL     | 6 mL             |                  | 6 mL                   |                 | 6 mL            | 6 mL            | 6 mL            | 6 mL            | 6 mL           | 6 mL      |
| Blood volume (approx.)                                               | 15 mL     | 16 mL  |       | 16 mL   | 16 mL    | 16 mL            |                  | 16 mL                  |                 | 16 mL           | 16 mL           | 16 mL           | 16 mL           | 16 mL          | 16 mL     |

- 1 If visit 5 (second vaccination) is delayed, participants will be invited to attend at week 4 (visit 4a) for an AE assessment, routine bloods and serology selecting the **unscheduled visit option on the worksheets/eDC**. Visit 4b can take place on the phone. If delayed, the window around the second vaccination can be wider -14/+28 days (weeks 12–20). **Visit 5 worksheets and eDC should only be used for the second vaccination visit as they activate the diary**. Visits 5a, 6, 7 and 8 will be 2d, 7d, 14d and 28d after the second vaccination; visit 9 at week 22. Visit 10 is not needed.
- 2 Haemoglobin, lymphocytes, neutrophils, platelets, creatinine, AST/ALT, ALP, total bilirubin, non-fasting glucose throughout. GGT at screening only.

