### 6.1 TRIAL ASSESSMENT SCHEDULE

The assessments in clinic and online, samples and volumes to be collected are outlined in **Table 2 Trial Assessment Schedule for the dose escalation and evaluation, both cohorts, and Table 3 Trial Assessment Schedule for the expanded safety cohort**. The maximum blood volume drawn from a participant in the dose escalation or evaluation parts, who completes 52 weeks of follow-up in the study period, is approximately 372 mL. The corresponding volume for participants in the expanded safety evaluation is 175 mL. These volumes do not include the blood volume that would be required if additional diagnostic tests are needed or safety tests have to be repeated. The required volumes per visit together with sample collection and processing guidelines are described in detail in the Laboratory Manual.

The visits in the trial assessment schedule are: a screening visit (Visit 1); an enrolment visit which must take place within 6 weeks of the screening visit and is defined as Week 0 (Visit 2); injection visits at Weeks 0 and 4 or 14 (Visits 2 and 5); safety visits at Weeks 1, 2, 5, 6, 8, 12 and 24 (Visits 3, 4, 6, 7, 8, 9 and 10) and a final visit at Week 52 (Visit 11). The visit windows are provided in **Tables 2 and 3**.

If the second injection which is scheduled at Visit 5 (week 4) is delayed pending a Trial Steering Committee recommendation on the dose to administer, a Visit 4a should be conducted at week 4 instead in order to record any adverse events, collect routine laboratory tests and serology. **The unscheduled visit option should be selected on the Visit Worksheet and eDC screens.** Study staff should maintain contact with participants and one further visit may be required, Visit 4b. This can be conducted over the phone. **The unscheduled visit option should be selected on the Visit Worksheet and eDC screens.** When participants attend for their delayed second injection, study staff should use Visit 5 worksheets and eDC screens which activate the participant diary. **Study staff must not use the Vaccination Visit Worksheet for week 4 or the week 4 eDC screens before the second injection visits.**

Information on vaccine reactions will be solicited directly from participants for one week following each injection using the participant facing tools in the eDC system. They will also be contacted, by telephone, 2 days after each injection.

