### 9.2 OUTCOME MEASURES

The outcome measures are:

- Solicited local injection site reactions starting within 7 days of administration of the vaccine: pain, tenderness, erythema, swelling
- Solicited systemic reactions starting within 7 days of administration of the vaccine: pyrexia, fatigue, myalgia, headache, chills, arthralgia
- Unsolicited adverse reactions (ARs) throughout the study period (including serious ARs)
- Serious Adverse Events
- Unsolicited adverse events throughout the study period
- The titre of serum neutralising antibodies 2 weeks after the second vaccination in the SARS-CoV-2 pseudovirus-based neutralization assay
- The titre of vaccine-induced serum IgG binding antibody responses to the SARS-CoV-2 S glycoprotein 2 weeks after the first and second vaccinations

The exploratory outcome measures are:

- Cell-mediated vaccine-induced immune responses measured by T- and B- cell ELISpot in participants in the dose escalation and evaluation parts
- Cell-mediated vaccine-induced immune responses measured by flow cytometry and intracellular cytokine staining in participants in the dose escalation and evaluation parts
- The profile of class and sub-class of antibody response
- Laboratory markers of infection and infection-induced immunity

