## Immunogenicity

In the first cohort, a total of 105 participants will be included in the randomised dose evaluation of immunogenicity, 35 at each dose. The primary analysis will compare SARS-CoV-2 neutralization IC50 values at 6 weeks (2 weeks after the booster at 4 weeks). Data on mice and recovered COVID-19 patients indicate a standard deviation of approximately 1.5 for neutralization log10 IC50 values. The sample size calculation for the dose evaluation part of this study is based on testing the slope coefficient in a linear regression, using the log10 scale for dose. The study has 97% statistical power (2α=0.05) to detect a true difference of 0.7 (log10 IC50 scale) between adjacent doses (corresponding to a slope of 1.4), 91% power a difference of 0.6, 79% power a difference of 0.5, and 59% power a difference of 0.4.

Data on the first and second cohorts will be considered together to explore the overall relationship between immunogenicity and dose, using the same primary endpoint. As it is suspected that the relationship will be non-linear over this wide dose range (100-fold), evaluation of statistical power is not possible without strong assumptions.

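### Table 2 and Section 5.1.5 date the Week 6 sample from enrolment, but the primary titre is defined as 2 weeks after a boost that may be given on any of Days 24 to 38; the two anchors are not reconciled.

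*Protocol*

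**What the plan says.** **Enrolment as anchor.** Protocol Section 5.1.5 states: "Target visit dates (based on the enrolment date) should be adhered to as far as possible", within the windows of Tables 2 and 3. For Groups A and B, Table 2 gives Visit 5 (boost) as Day 28, -4 to +10; Visit 5a as Day 30 with no window; Visit 6 as Day 35, 0 to +2; Visit 7 as Day 42, -2 to +2; Visit 8 as Day 56, -4 to +4; and Visit 9 as Day 84, -7 to +7. No footnote to Table 2 moves the later visits when the boost moves.

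**Second vaccination as anchor.** Section 9.2 defines the outcome as "The titre of serum neutralising antibodies 2 weeks after the second vaccination". Section 9.3 takes the primary comparison at Week 6 and treats the two as the same: "values at 6 weeks (2 weeks after the booster at 4 weeks". Section 6.1 says of participants: "They will also be contacted, by telephone, 2 days after each injection". Section 6.4 places an examination one week after each vaccination.

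**Where the protocol re-dates visits.** Table 3 footnote 1 does so for Group C participants who delay the boost: "Visits 5a, 6, 7 and 8 will be 2d, 7d, 14d and 28d after the second vaccination; visit 9 at week 22". The same footnote says "the window around the second vaccination can be wider -14/+28 days" and glosses this as Weeks 12 to 20. Section 5.1.5, in its text on trial-wide pauses, adds: "Missed injections will be rescheduled and the remaining study visits rescheduled/repeated accordingly".

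**The concern.** The two anchors agree only when the boost is given close to Day 28. A site can give the boost inside its window, take Visit 7 inside its window, record no deviation, and still draw the primary sample well away from 14 days after the boost.

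That matters because the Week 6 titre is the measure on which doses are compared. Variation in time since boost adds noise to the slope on dose. If boost timing differed by dose or cohort, it could also distort the comparison. Section 9.3 considers the two cohorts together, and under Section 9.1 the second cohort is not individually randomised and runs at two or more sites, so randomisation would not balance such a difference.

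The post-boost safety contacts have the same problem. On Table 2's printed days, the call and the diary review that are meant to follow the boost can be scheduled before it.

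**Working it through.** **Inputs.** Visit days and windows come from Table 2, the outcome definition from Section 9.2, and the power inputs from Section 9.3 (35 per dose; doses 0.1, 0.3 and 1 µg; SD 1.5; two-sided 0.05).

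**1. The plan's own interval.** Nominal Visit 7 minus nominal Visit 5 is 42 - 28 = 14 days, which reproduces the stated 2 weeks.

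**2. Permitted days.** Boost: 28 - 4 = 24 to 28 + 10 = 38. Visit 7: 42 - 2 = 40 to 42 + 2 = 44.

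**3. Days from boost to each visit, each window read on its own.** Minimum = earliest visit day - 38; maximum = latest visit day - 24.

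| Visit | Permitted days | Days after boost |
|---|---|---|
| V6 | 35 to 37 | 35 - 38 = -3 to 37 - 24 = 13 |
| V7 | 40 to 44 | 40 - 38 = 2 to 44 - 24 = 20 |
| V8 | 52 to 60 | 52 - 38 = 14 to 60 - 24 = 36 |
| V9 | 77 to 91 | 77 - 38 = 39 to 91 - 24 = 67 |

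**4. Requiring visits to follow the boost.** If Visit 6 must come after the boost, the latest boost is Day 36 and the Visit 7 minimum is 40 - 36 = 4 days. If the 2-day call must also fall no later than Visit 6, the latest boost is Day 35 and the minimum is 40 - 35 = 5 days. The maximum stays at 20.

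**5. Which boost days can meet the definition.** A Visit 7 at exactly 14 days needs the boost on Days 26 to 30 (40 - 14 to 44 - 14). A Visit 7 at 12 days or more needs the boost no later than 44 - 12 = Day 32. Boosts on Days 33 to 38, which are 6 of the 15 permitted days, therefore allow no in-window Visit 7 at 12 to 16 days.

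**6. Counting from the actual boost.** With the existing -2/+2 tolerance, Visit 7 falls 12 to 16 days after the boost for everyone. A Day 24 boost gives Days 36 to 40, and a Day 38 boost gives Days 50 to 54.

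**7. Power.** The stated figures reproduce. For a t-test of the slope on log10 dose with 103 degrees of freedom and slope = 2 × the adjacent-dose difference, power is 97.2%, 91.2%, 78.9% and 59.9% for differences of 0.7, 0.6, 0.5 and 0.4 (stated: 97%, 91%, 79%, 59%). The loss from mistiming cannot be computed, because the protocol gives neither the distribution of boost dates nor how fast titres rise.

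For illustration only, assume boost and Visit 7 days uniform over their windows (interval SD 4.55 days) and a rise of 0.02 to 0.2 log10 per day. The SD becomes √(1.5² + (0.02 × 4.55)²) = 1.50 to √(1.5² + (0.2 × 4.55)²) = 1.75. Power at a difference of 0.5 then lies between 79% and 66%. The range runs from no loss to a material one, and every input to it is assumed.

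**8. Table 3 footnote 1.** Week 14 minus 14 days is Week 12, and Week 14 plus 28 days is Week 18. Section 1.4.1 also gives an interval of 4 to 18 weeks, but the footnote prints an upper end of Week 20. Visit 8 is 28 days after the boost. A Week 18 boost puts Visit 8 at Week 22, the same week as the fixed Visit 9. A Week 20 boost puts Visit 8 at Week 24, after Visit 9.

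**The case against.** **Is enrolment really the rule?** A reader might infer that the protocol settles on enrolment as the anchor. It does not. The outcome definition, the telephone call and the one-week examination all count from the injection. The printed windows after the boost repeat those after the first vaccination, which suggests the same spacing was intended. Section 5.1.5 also moves later visits after a missed injection, and its deferral paragraph points ahead to text on missed visits. This part of the objection stands: the defect is a contradiction. It does not remove the problem. An injection on Day 38 is in window and so is not clearly missed, and the window that the deferral paragraph promises is not given in the text that follows it.

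**Is the 2-day extreme credible?** A reader might take 2 days as a realistic sampling time. It needs a Day 38 boost with Visits 5a and 6 on their printed days, both before the injection they follow. Sections 6.1 and 6.4 rule that out in substance. A range of 4 to 20 days is the more defensible statement.

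**Is there a known loss of power?** A reader might infer a specific loss, for example by supposing that some fraction of Week 6 sera carry no dose effect. No such fraction is in the documents, and participants were already primed at the same dose. Nor do the documents show that deferral differed by dose.

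**Can re-dating rescue the powered comparison?** No. Section 6.8 records that A1 and B1 have all completed Visit 9. An unseen SAP may set analysis windows, but it cannot re-time samples already drawn.

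**Conclusion.** The point holds as an unreconciled contradiction about when the primary immunogenicity sample is taken. Section 5.1.5 and Table 2 allow a compliant Visit 7 at 4 to 20 days after the boost (2 to 20 if the windows are read in isolation), against a definition of 14 days. No in-window sample at 12 to 16 days is possible for boosts on Days 33 to 38. These figures are arithmetic on the printed windows and describe what is permitted, not what happened; actual boost and sampling dates are not in the documents. The effect on power and on bias between doses is unknown.

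The footnote 1 discrepancies are separate. They concern delayed Group C, whose Visits 5a to 8 are already dated from the boost, and they add no weight to the Week 6 dose comparison.

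**What to change.** **Participants still in follow-up (A2, B2, remaining Group C).** State in Tables 2 and 3 and Section 5.1.5 that Visits 5a, 6, 7, 8 and 9 are counted from the actual second vaccination, at 2, 7, 14, 28 and 56 days (84 - 28 = 56 for Visit 9), with the existing tolerances. Footnote 1 already does this for Visits 5a to 8 in delayed Group C. In Section 5.1.5, supply the window that the deferral paragraph refers to, or correct the cross-reference.

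**Groups A1 and B1.** Keep all eligible Visit 7 samples in the primary analysis. Tabulate actual days since boost by dose. Add a sensitivity analysis that adjusts for days since boost, or is limited to samples at 12 to 16 days. That restriction should not become the primary analysis, because it selects randomised participants on something that happens after randomisation and reduces the sample.

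**Table 3 footnote 1.** Reconcile the -14/+28 day window with the printed week range and with Section 1.4.1, and reconcile the fixed Visit 9 with Visit 8 for late boosts.

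**Cost.** A line in each table, short edits to Section 5.1.5 and the footnote, and one tabulation and one sensitivity analysis from dates already recorded. No extra visits or samples are needed.
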